### Screening/inclusion of patients

At the screening visit (visit 1), all patients will be treated according to the standard of care. SoC as described in this protocol follows general guidance and will be carefully applied by all study sites, and all patients have to wear off-loading footwear throughout the whole study. Particularly in the performance of wound cleaning and debridement, the investigators receive additional guidance in the investigator brochure and a training during the site initiation visit. A run-in period of at least 2 weeks will allow assessments of wound area reduction based on optimized SoC. The change of wound area must not exceed 30% between screening visit and randomization visit (14–28 days) to ensure only hard-to-heal DFUs are included into the study. Wound imaging and wound size measurement will be performed using the eKare inSight wound imaging (eKare, Fairfax, VA, USA) at the site level. Data are uploaded to a data management platform and centrally adjudicated by two blinded evaluators. Data for the primary efficacy endpoint will be calculated based on the data generated by the central adjudication assessment. An electronic case report form (eCRF) will be used for this study, and entries and corrections will be performed only by study site staff authorized by the investigator. After all eCRF pages have been reviewed by a monitor and all queries resolved, a final review will be performed by the data review team consisting of the monitors, the data manager, and the medical data reviewer, before database lock during a blinded data review meeting.

A special section is designated to adverse events (AEs) in the eCRF. All AEs will be reported within the annual Development Safety Update Report (DSUR). In the case of a serious AE (SAE), the investigator must complete the SAE report form, the automated eCRF reporting system forwards the SAE report to the drug safety department at the CRO, and the sponsor is informed. SAEs and SUSARs will be reported to the EC and the regulatory agencies according to legal requirements.

The monitor will contact and visit the investigator regularly (as defined in the Monitoring Plan) and will be granted access to all source documents needed to verify the entries in the eCRF and other protocol-related documents, provided that patient confidentiality is maintained in agreement with local regulations. There is no Trial Steering Group implemented in that trial as it was considered a low-risk intervention.

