### Standard study procedures

Before inclusion of a patient into the study, written informed consent will be obtained after disclosure of all aspects of the trial by a physician. The investigator will verify that all inclusion, exclusion, and randomization criteria are met, and all other requirements of the study protocol are fulfilled. The eligibility criteria are listed in Table 2. Patients will be enrolled in various clinical settings, including outpatients from specialized wound management clinics and inpatients from tertiary care setting. The visit schedule is shown in Table 3. On the informed consent form, participants will be asked if they agree to the use of their data: medical findings and personal information will be collected and written down in their personal file at the site; a transfer of the data, in particular to the sponsor, takes place only in pseudonymized and encrypted form. This trial does not involve collecting biological specimens for storage. During their participation in the clinical study, patients will be insured as defined by legal requirements.

**Table 2 Tab2:** Inclusion/exclusion criteria

Inclusion criteria	
○ Patient is between 18 and 80 years of age	
○ Patients with type I or type II diabetes with a glycosylated hemoglobin (HbA1c) of ≤ 12%, obtained at enrollment or within 30 days prior to study enrollment	
○ Patients who have a wound defined as diabetic foot ulcer present for ≥ 4 weeks	
○ Foot ulcer Wagner grade I–II or ARMSTRONG grade I-A (superficial, non-infected, non-ischemic wound not involving the tendon, capsules, or bone) or II-A (non-infected, non-ischemic wound penetrating to tendon or capsule but not to the bone or joint)	
○ Estimated foot ulcer surface area between ≥ 1 and ≤ 8 cm^2^ as measured at the day of randomization assessed using the eKARE imaging and measurement device	
○ A patient with more than one diabetic foot ulcer may be included in the study but only one ulcer will be selected for the investigational treatment based on investigator judgment as far as the ulcer meets the inclusion criteria (the largest ulcer fitting the inclusion criteria will be selected as index ulcer)	
○ Wound area has not changed by more than 30% between screening visit and randomization visit (at least 14 days)	

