Days from randomization visit	Days -14 to -28 (prior to active treatment)	Day 0	Day 1 to day 28	Day 30 (± 5 days)	Day 44 (± 2 days)	Day 56 (± 2 days)	Day 84 (± 5 days)

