### Statistical analysis

For the preceding safety lead-in part of the study, safety data of 12 randomized patients will be summarized after the 4-week treatment period. These data will be evaluated by the DSMB. Unblinding is not planned but is possible if requested by the DSMB. Safety and efficacy results of the safety lead-in phase will be included in the data pool of the entire clinical study for final analysis (i.e., the safety lead-in phase is an integral part of the entire MARSYAS II study).

The main study is designed to evaluate the dose-response relationship for clinical efficacy of topical APO-2 at three dose levels compared to placebo. The minimum effective dose, which is defined as the smallest dose with a discernible, useful effect, will be determined.

The primary endpoint is the assessment of the dose-related, relative reduction in wound area from baseline to week 4 (continuous endpoint). Analysis of the primary and secondary efficacy variables will be based on the full analysis set (i.e., all patients with a measured wound size at baseline, who received at least one dose of IMP and have data available at the end of treatment visit). Details are defined in a statistical analysis plan. If data are normally distributed, one-way analysis of variance (ANOVA) will be calculated, including a Dunnett multiple comparison post hoc test, to test each of the active doses against placebo. If Gaussian distribution is not given, a non-parametric Kruskal-Wallis test with Dunns post hoc tests will be performed. If at least one of the doses is statistically significant, then the dose-response relationship is established. In addition, a dose-response model will be developed and tested. Three candidate models (linear, quadratic, and logistic) will be fitted to the data and the Akaike Information Criterion will be used to select the best model. Confidence bands for the estimated dose-response curve will be presented. Binary endpoints will be analyzed by displaying the number and percentage of patients in each dose group. Differences among dose groups will be tested using Fisher’s exact test. For the evaluation of the continuous endpoints, data will be analyzed as absolute values and changes from baseline will be represented by basic statistics (mean, standard deviation, minimum, first quartile, median, third quartile, maximum). A detailed description of the reports and tests is specified in a statistical analysis plan.

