## Discussion

The clinical trial MARSYAS II will be the first clinical trial testing the safety and efficacy of allogeneic secretome of white blood cells in patients with DFU. A phase I trial named MARSYAS I testing autologous APOSEC in ten healthy male subjects was already successfully performed and showed no severe or serious adverse events [31]. As the drug tested in MARSYAS I was autologous and some modifications, such as viral depletion steps, were added to the manufacturing process of the allogeneic APOSEC which will be tested in MARSYAS II, the two studies cannot be compared from a regulatory point of view. Therefore, a safety lead-in first in man phase will precede the main study of the clinical trial to observe the safety and tolerability of allogeneic APOSEC. However, based on data obtained by non-clinical pharmacology and toxicology studies and the phase I trial, we believe that the product is safe.

Wound area reduction in clinical trials, if prospectively defined, indicates relevant biological activity and therefore was chosen as the primary endpoint. Secondary endpoints will help planning subsequent pivotal phase III trials where the primary endpoint has to be complete wound closure. Several randomized controlled trials and cohort studies have shown a strong correlation between wound area reduction at 4 weeks and complete wound closure at 12 or 20 weeks. In studies where wound area reduction was used as an endpoint, a predefined > 50% reduction in the initial area was considered clinically relevant [32–34]. Therefore, the proportion of patients showing a > 50% reduction of the initial wound area is proposed as a secondary endpoint [35]. The run-in period of 14 to 28 days is performed to determine if the wounds heal under standard of care including off-loading footwear. This procedure is implemented to include hard-to-heal wounds and to exclude wounds that are just mistreated. In that case, such patients will not be included in our study.

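### The primary one-way ANOVA omits the wound-size stratum and the measured run-in change, although an unscaled 30% run-in limit lets the maximum entry healing rate vary about twofold with run-in length

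*Protocol article*

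**What the plan says.** Under Screening/inclusion of patients, the protocol article states: "The change of wound area must not exceed 30% between screening visit and randomization visit". The interval given there is 14 to 28 days, and the purpose is "to ensure only hard-to-heal DFUs are included into the study". Table 2 repeats the 30% figure with only a 14-day minimum. The visit schedule (Table 3) gives the same 14-to-28-day window, and the Discussion confirms it: "The run-in period of 14 to 28 days is performed to determine if the wounds heal under standard of care including off-loading footwear". Nowhere is the limit turned into a rate per unit of time.

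Table 3 has wound size measured with the eKare device at visit 1 and at visit 2. Main-study randomisation is stratified by wound size, with at least a third of patients above 4 cm².

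The primary endpoint, under Statistical analysis, is the relative area reduction from baseline to week 4. If the data are normally distributed, "one-way analysis of variance (ANOVA) will be calculated", with Dunnett comparisons against placebo; otherwise Kruskal-Wallis with Dunn's tests is used. No covariate or stratification factor is named.

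**The concern.** A percentage change over an interval that can double in length does not define a healing rate. A wound close to the limit after two weeks is healing about twice as fast as one close to the limit after four, yet both count as hard to heal. Recent healing speed on standard care is a plausible predictor of healing over the next four weeks, so patients with different outlooks are pooled in each arm.

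The trial records the information needed to account for this, but a one-way ANOVA cannot use it. It also leaves out the factor on which randomisation is stratified. Variation that either variable could explain stays in the error term, and chance imbalance between small arms goes uncorrected. What is at stake is precision and the description of the enrolled population, not the validity of the randomised comparison.

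**Working it through.** **Inputs from the protocol.** Run-in limit 30%; run-in 14 to 28 days; assumed 4-week reductions 40%, 45%, 50% and 55%; within-group SD 0.156; two-sided alpha 0.05; power 80%; stated minimum 23 per group; 132 patients in total, of whom 12 are in the lead-in; equal allocation in the main study. **Assumed, because the documents do not give it:** the correlation ρ between the run-in rate and the 4-week outcome, shown from 0.2 to 0.5.

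**1. The plan's own figure.** The variance of the four means about 0.475 is V = (0.075² + 0.025² + 0.025² + 0.075²)/4 = 0.003125, printed as 0.003. For a four-group F-test the noncentrality is λ = 4nV/SD², with 4(n − 1) error degrees of freedom.
- n = 22: λ = 0.275/0.024336 = 11.30, power 79.5%.
- n = 23: λ = 0.2875/0.024336 = 11.81, power 81.5%.

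The stated 23 is reproduced. With V rounded to 0.003, power at 23 is 79.8% and the minimum becomes 24, a rounding difference.

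**2. Maximum permitted entry rate.**

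| Run-in | Constant proportional healing, per week | Linear healing, per week | Projected 4-week reduction, proportional / linear |
|---|---|---|---|
| 14 days | 1 − 0.7^(1/2) = 16.3% | 0.30/2 = 15% | 1 − 0.7² = 51% / 60% |
| 28 days | 1 − 0.7^(1/4) = 8.5% | 0.30/4 = 7.5% | 30% / 30% |

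The ratio is 16.3/8.5 = 1.9 (proportional) or 15/7.5 = 2.0 (linear). At the limit, the shorter run-in admits a wound projected to do better than the plan's 40% placebo response; the longer one does not.

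**3. Power with the run-in rate as covariate.** The residual SD becomes 0.156·√(1 − ρ²), so λ is divided by (1 − ρ²). Two further error degrees of freedom are charged, one for the rate and one for the stratum. No gain is credited to the stratum. For example, at n = 23 and ρ = 0.3, λ = 11.81/0.91 = 12.98.

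The second sample size is (132 − 12)/4 = 30 per arm, where unadjusted λ = 0.375/0.024336 = 15.41. It makes no allowance for dropout and does not add the lead-in patients back.

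| ρ (assumed) | Power, 23 per arm | Power, 30 per arm |
|---|---|---|
| unadjusted | 81.5% | 91.5% |
| 0.2 | 83.2% | 92.6% |
| 0.3 | 85.3% | 93.9% |
| 0.4 | 88.2% | 95.6% |
| 0.5 | 91.8% | 97.4% |

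A third degree of freedom changes these figures by less than 0.1 point.

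**4. Chance imbalance.** The part of an unadjusted two-arm difference that comes from imbalance in the run-in rate has standard error ρ·0.156·√(2/n). At n = 23 this is 0.9 points for ρ = 0.2 and 2.3 points for ρ = 0.5. The planned step between adjacent doses is 5 points.

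**The case against.** **No contradiction and no bias.** The sections agree on 30% and on 14 to 28 days. A reader might infer that the arms are not comparable. They are, in expectation: run-in length is settled before blinded randomisation. This stands in full.

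**Mean entry rates.** A reader might also infer that patients' actual entry rates differ twofold by run-in length. Only the maximum does so by arithmetic. The mean ratio depends on a rate distribution that the documents do not give. In simulations with normal weekly log-rates (assumed mean 0.05 to 0.20, SD 0.05 to 0.15) it ran from 1.5 to 2.7, and it did not hold when the mean rate was zero.

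**Spread of admitted wounds.** Because the limit applies to change in either direction, projected 4-week change at entry runs from 51% shrinkage (1 − 0.7²) to 69% growth (1.3² − 1). It is tempting to blame the variable window for this span, but all of it arises at 14 days. A fixed 14-day run-in would give the same range; longer run-ins only narrow it.

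**Wounds at the placebo rate.** One could say that a wound healing at the plan's placebo rate is admitted or refused according to visit timing. At day 14 it has shrunk 22.5% (proportional) or 20% (linear), and at day 28 by 40%, so the two ends do differ. At day 21 the answer depends on the model: 31.8% fails, while a linear 30% does not exceed the limit. The illustration also applies an assumed on-treatment response to the run-in.

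**Size of the gain.** Truncation at 30% narrows the covariate and lowers ρ. The visit 2 area ends the run-in and is also the outcome baseline, so its measurement error enters the two with opposite signs and lowers ρ further. And 23 per arm is the stated minimum; at about 30 the unadjusted test already has 91.5% power on the plan's inputs. All of this stands and makes the benefit modest.

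**Deferral to the SAP.** The protocol leaves details to a statistical analysis plan that is not shown, and an unadjusted test is valid in an exploratory randomised trial. But the protocol does name the method, and a one-way ANOVA has no covariates. Deferral therefore does not remove the point, though it may already have been settled there.

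**Conclusion.** The point holds as one of precision and of a loosely defined population. The unscaled 30% limit makes the maximum permitted entry rate 1.9 to 2.0 times higher after a 14-day than after a 28-day run-in. The named primary analysis uses neither the stratification factor nor the run-in change already measured.

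The documents do not support reading this as bias, as an invalid test or as an underpowered trial. For an assumed ρ of 0.2 to 0.5, adjustment adds about 2 to 10 points of power at 23 per arm (81.5% to 83–92%) and about 1 to 6 points at 30 per arm (91.5% to 93–97%), and the low end may be the more likely. These are F-test figures, not Dunnett power, and rest on the plan's SD of 0.156 and its assumed reductions. The change is worth making because it needs no new data.

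**What to change.** Pre-specify an ANCOVA for the 4-week relative area reduction, with treatment group and these covariates:
- the wound-size stratum, or log area at visit 2;
- the run-in log-rate, ln(area at visit 1 / area at visit 2) divided by the run-in days.

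Make the Dunnett comparisons on the adjusted means, and say how the adjustment carries over to the non-parametric branch. The cost is two degrees of freedom, or three if both the stratum and log area are used, plus analysis-plan wording that replaces the one-way ANOVA. No visit or measurement is added.

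Separately, the sponsor should reconcile the single 30% limit over a 14-to-28-day interval with its stated aim of admitting only hard-to-heal ulcers. Any change there needs a short amendment. No threshold is proposed here; the entry rule is for the sponsor to set.

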### Dosage of the investigational medicinal product

APO-2 will be applied to patients in three different dosages: low dose (12.5 U/ml), medium dose (25 U/ml), or high dose (50 U/ml). In the control group, the patients will be treated with placebo which is the vehicle of APOSEC (the culture medium used for APOSEC production which is processed like APOSEC including viral inactivation but without cells and therefore without the secretome which represents the active ingredient of the verum). 0.5 ml IMP will be applied per cm^2^ wound surface area for each dose group with a maximum of 4 ml gel on an 8-cm^2^ wound. Therefore, the minimum dose applied in this study will consist of 6.3 U/wound/treatment and the maximum dose applied will be 200 U/wound/treatment (Table 4).

**Table 4 Tab4:** Dosage in MARSYAS II and toxicological studies

						Maximum doses in toxicological studies		
	Concentration [U/ml]	Area dose [U/cm^2^]	Maximum area dose [U/cm^2^]	Dose [U/kg b.w.]	Dose [U/kg b.w.]	Dose [U/kg b.w.]	Dose [U/kg b.w.]	Dose [U/kg b.w.]
		Units per 1 cm^2^	Units per 8 cm^2^	Minimum dose per 1 cm^2^	Maximum dose per 8 cm^2^	Single dose i.v. rats	4 weeks repeated dose i.v. mice	4 week repeated dose s.c. minipigs
Low dose	12.5	6.25	50	0.104	0.833			
Medium dose	25.0	12.5	100	0.208	1.667			
High dose	50.0	25	200	0.417	3.333	500	500	33.3

Minimum dose/wound treatment, 6.25 U/cm^2^. Maximum dose/wound treatment, 200 U/8 cm^2^

*U* Units, *b.w.* body weight, *i.v.* intravenous, *s.c.* subcutaneous

The IMP will be prepared by unblinded pharmacists at the study sites. The information which IMP is dedicated to which patient is generated in the eCRF and can be retrieved by the pharmacist. Clear instructions for preparation based on standard operating procedures and videos are provided by the sponsor. Blinding of the investigator and the patient is assured by the appearances of the IMP (different doses of APO-2 or placebo) which is in each case the same, and the paper-based communication between the sites and the pharmacies as well as the electronic documentation (and the user rights) in the eCRF is strictly regulated. Also, the sponsor and the statisticians remain blinded until the end of the study. Unblinding in the case of an emergency is possible both in the eCRF or paper based (envelopes at the study site) by the investigator or by the pharmacovigilance in case of a suspected unexpected adverse drug reaction.

### Study endpoints

The primary endpoint is wound area reduction after 4 weeks of treatment with APO-2, i.e., wound area at visit 14 (end of treatment visit) compared to visit 2 (randomization). Secondary endpoints are > 50% reduction in wound area after 4 weeks (binary outcome); wound size at baseline and 1, 2, 3, 4, 6, 8, and 12 weeks after the first application of IMP; proportion of patients with complete wound closure during the 12-week follow-up period (100% re-epithelialization of the wound surface with the absence of drainage); time to complete wound closure; recurrence rate of the ulcer during the 12-week follow-up period; clinical assessment of peripheral neuropathy at baseline, 4, and 12 weeks after the first application of IMP; number of patients with local adverse events or serious adverse events (SAEs) with causal relationship to study medication; evaluation of wound pain by visual analogue scale (VAS) at baseline, at every treatment visit, and 4, 6, 8, and 12 weeks after the first application of IMP; and evaluation of quality of life using Wound QoL questionnaire at baseline, 4, and 12 weeks after the first application of IMP.

Patients who discontinue the trial prematurely after having received at least one dose of IMP will be regarded as “early termination,” and the circumstances and reasons of their discontinuation must be documented in the eCRF. All effort should be done to follow-up with the patient visit schedule as per protocol, but at least a complete end-of-treatment examination should be performed.

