## Background

According to the World Health Organization (WHO), diabetes is on the rise: the number of persons suffering from diabetes increased from 108 million in 1980 to 422 million in 2014. The global prevalence of diabetes among adults over 18 years of age has risen from 4.7% in 1980 to 8.5% in 2014 [1]. Major complications of diabetes mellitus are the development of foot ulcers and impaired wound healing. The International Working Group on the Diabetic Foot defines a foot ulcer as a full-thickness wound involving the foot or ankle [2]. Non-healing, chronic wounds predominantly remain in early inflammatory stages of wound healing, lacking the controlled synchronization and succession of events that lead to rapid and complete healing. With regard to diabetic ulcers, healing impairment is caused by several intrinsic factors (neuropathy, vascular problems) and extrinsic factors (wound infection, callus formation, and excessive pressure to the site). By definition, this set of predisposing abnormalities in diabetes has been referred to as the “pathogenic triad” of neuropathy, ischemia, and trauma. One abnormality in the wound healing process can lead to another, generating a pathogenic vicious circle in diabetes [3]. Despite better understanding of the underlying disease pathology and improved care of diabetic foot ulcers (DFUs), foot complications are still the most frequent reasons for hospitalization of diabetic patients [4]. Delayed healing of DFU and further related problems (e.g., neuropathy and unnoticed injuries, tissue necrosis, sepsis) are the primary factors leading to lower extremity amputation and death. Moreover, about 50% of patients undergoing foot amputation develop an ulcer in the contralateral limb within 18 months of surgical intervention [5]. Nearly half of all unhealed neuropathic ulcers lead to death within 5 years [6]. In spite of the severe consequences of DFU, no effective medicinal product for treating non-healing ulcers is currently available.

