## Methods/design

### Study setting

The clinical study protocol (CSP) of the MARSYAS II trial was written in accordance with the Recommendations for Interventional Trials (SPIRIT) guidelines and completing the SPIRIT Checklist (see supplemental file). The study was approved by the Austrian health authorities (Austrian Office for Safety in Health) and the local Austrian ethics committees (Linz and Klagenfurt). A thorough feasibility and site qualification was performed prior to the selection of 16 study sites in 4 countries (Austria, Germany, Poland, and the Czech Republic) to ensure the achievement of adequate participant enrollment to reach the calculated target sample size. The clinical research organization (CRO) FGK Clinical Research GmbH (Munich, Germany) and its subsidiaries in the Czech Republic and Poland will coordinate the centers and are responsible for data management and pharmacovigilance. Any protocol modifications will be timely reported to the respective authority.

The primary objective of the MARSYAS II trial is to determine the dose-response relationship of the clinical efficacy of APO-2 multiple dose administration in patients with diabetic foot ulcer at three different dose levels compared to placebo. The secondary objectives are to evaluate the safety and tolerability of APO-2 at three different doses and to generate data on additional clinical endpoints for the conception of a phase III study.

The study design is shown in Fig. 1. The partners of the safety lead-in phase are listed in Table 1.

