**Assessments**							
**Physical examination and vital signs**	X	X		X			X
**Hematology**^a^	X						X
**Serum chemistry**^b^	X						X
**Urine analysis**^c^	X						X
**Urine pregnancy test**	X	X		X			
**Wound assessment**	X	X	X	X	X	X	X
**Assessment of wound closure**	X	X	X	X	X	X	X
**Wound size measurement (eKare inSight®)**	X	X	X	X	X	X	X
**Standard of care for wound management**	X	X	X	X	X	X	X
**VAS—score for pain**	X	X	X	X	X	X	X
**Neurological assessment foot**		X		X			X
**Chronic wound quality of life questionnaire**		X		X			X
**Recording adverse events**		X	X	X	X	X	X

^a^Erythrocytes/leucocytes/hemoglobin, hematocrit, thrombocytes, MCV, MCH, and MCHC

^b^Sodium, potassium, total protein, albumin, BUN, creatinine, glucose, Hba1c, AST, ALT, GGT, total bilirubin, and CRP

^c^Urine dip stick: pH, nitrite, glucose, leucocyte, ketone, bilirubin, protein, and blood

In the safety lead-in period, a minimum of 12 patients will be enrolled and randomly assigned (3 active: 1 placebo) to receive the medium dose of APO-2, (25 U/ml, 9 patients) or placebo (3 patients). Randomization is done by computer-generated random numbers, and the information is only given to the pharmacist who prepares the IMP. Safety assessments of patients in the safety lead-in period will include recording of adverse events (AEs), use of concomitant medications, and wound size measurement. Immediately after the last randomized patient reaches the end of treatment with IMP, safety and efficacy data of the safety lead-in period will be reviewed by an independent Data and Safety Monitoring Board (DSMB). During this evaluation, study enrollment will be paused and only the active patients will be followed up. The DSMB board consists of three independent experts in the field of clinical wound care and one statistician.

After a review of the safety results, the DSMB will make a recommendation as to whether or not the main study may start as designed (i.e., randomized, double-blind, parallel group). The DSMB may also recommend the inclusion of additional patients in the safety lead-in period prior to initiation of the main study. After the DSMB decision, the patients in the safety lead-in period will continue to be followed as per protocol completing the 8-week follow-up period after the last administration of the investigational product. Besides the DSMB, no other interim analyses or formal stopping rules are intended.

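### The only adverse-event endpoint is narrower than the safety objective: non-serious systemic events cannot enter it, and systemic SAEs enter only if judged drug-related

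*Protocol article*

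**What the plan says.** Under Study setting, the objective carries no limit to local or related events: "The secondary objectives are to evaluate the safety and tolerability of APO-2 at three different doses".

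Under Study endpoints, the adverse-event item in the list of secondary endpoints is the "number of patients with local adverse events or serious adverse events (SAEs) with causal relationship to study medication". No other listed endpoint counts adverse events. Wound pain and quality of life are listed, but they would not register a systemic reaction or an infection as such.

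The Background names tissue necrosis and sepsis among the problems that "are the primary factors leading to lower extremity amputation and death".

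Collection is broader than the endpoint. Table 3 records adverse events at every visit from visit 2 to visit 17. For the lead-in, the text below that table says: "Safety assessments of patients in the safety lead-in period will include recording of adverse events (AEs), use of concomitant medications, and wound size measurement". Under Screening/inclusion of patients, all AEs go into the annual safety update report, and SAEs go to the CRO's drug safety department and the sponsor.

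For binary endpoints, Statistical analysis gives number and percentage per dose group and adds: "Differences among dose groups will be tested using Fisher’s exact test". It leaves further reports and tests to a statistical analysis plan.

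**The concern.** The endpoint narrows the objective twice. By site, a non-serious event away from the wound, such as fever or a generalised allergic reaction, has no route in. By judgement, a systemic SAE needs an attribution to study medication first.

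That attribution is hard to make here. The disease offers a ready alternative explanation for sepsis or death. The Discussion describes the lead-in as the first human use of the allogeneic product, so investigators have little experience on which to base a case-by-case judgement. A placebo arm allows an excess to be seen as a difference in counts without deciding the cause of any single event. This endpoint applies the decision before the count.

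At stake is whether the pre-specified safety measure, which is meant to inform phase III planning, can show a dose-related excess of systemic events if there is one.

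**Working it through.** **The plan's own figure.** The document computes nothing for the safety endpoint. Its one sample size, 23 per group, is for wound area reduction. It reproduces with a one-way ANOVA F test with k = 4, SD = 0.156, alpha = 0.05 and noncentrality n × k × V / SD². With V = 0.003125, the variance of the assumed means 0.40, 0.45, 0.50 and 0.55 (divisor 4), n = 23 gives power 0.815. With the rounded V = 0.003, n = 24 is needed (power at 23 is 0.798). This has no bearing on safety.

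**What can enter the endpoint.** The closing causality phrase can be read in two ways.

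| Event | Causality applies to SAEs only | Causality applies to both |
|---|---|---|
| Local AE, any seriousness | counts whatever the cause | counts only if judged related |
| Systemic SAE | counts only if judged related | counts only if judged related |
| Systemic non-serious AE | never counts | never counts |

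The last two rows are the same under either reading. The first row is where the wording matters.

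**Illustration of the dilution.** All risks and shares below are assumptions.

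- Patients per arm: (132 − 12) / 4 = 30, taking the 12 lead-in patients out of the stated total of 132.
- Risks: true risk p0 on placebo and p1 on one dose, for SAEs that are subject to the causality condition.
- Share judged related: r, equal in both arms because the assessor is blinded.
- Expected counts: 30 × r × p1 against 30 × r × p0.
- Risk difference: r × (p1 − p0).
- Power: exact, two-sided Fisher test at 0.05, one dose against placebo, by binomial enumeration, counting only results where the active arm is worse.

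| p0, p1 | r | Expected patients, dose vs placebo | Difference (points) | Power |
|---|---|---|---|---|
| 10%, 40% | 1 (all-cause) | 12 vs 3 | 30 | 0.71 |
| 10%, 40% | 0.5 | 6 vs 1.5 | 15 | 0.24 |
| 10%, 40% | 0.25 | 3 vs 0.75 | 7.5 | 0.04 |
| 10%, 40% | 0.1 | 1.2 vs 0.3 | 3 | 0.001 |
| 10%, 30% | 1 (all-cause) | 9 vs 3 | 20 | 0.37 |
| 10%, 30% | 0.5 | 4.5 vs 1.5 | 10 | 0.09 |
| 10%, 30% | 0.25 | 2.25 vs 0.75 | 5 | 0.01 |

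**Pooled with the lead-in.** Statistical analysis puts the lead-in into the final data pool. All active patients then number 3 × 30 + 9 = 99, and placebo 30 + 3 = 33. For 10% against 40%, power is 0.94, 0.53 and 0.13 at r = 1, 0.5 and 0.25. For 10% against 30% it is 0.65, 0.26 and 0.03. The level rises, but the loss from the filter remains.

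The tables apply to local serious events only under the second reading. Under the first, those events stay at the r = 1 line.

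**The case against.** **The events are not lost.** This stands. They are recorded from visit 2, reported, and available to the monitoring board at the lead-in review. A reader might infer that an excess disappears from the trial, or that no all-cause comparison will be made. The document does not say so: all-cause tables by arm are ordinary content for an analysis plan that is not shown. The point is limited to what the endpoint is defined to count. A supporting table elsewhere would not change that definition.

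**The local limb already captures ulcer events.** If causality qualifies only SAEs, infection or necrosis at the index ulcer counts whatever its cause. It is therefore too strong to say that such events are necessarily filtered out. Osteomyelitis should not be cited as natural course on the strength of the Background, since it appears only among the exclusion criteria. What remains under that reading is the systemic events.

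**Attribution is blinded.** A reader might infer that the filter gives up the randomized comparison or favours active treatment. It does neither: the judgement is made without knowledge of the arm, and the filtered counts are still compared as randomized.

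**A causality filter removes background noise.** It would, if investigators could tell drug-caused events from disease-caused ones. The dilution figures assume that they cannot. Partial discrimination would reduce the loss.

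**The risks are invented, and the trial is small and exploratory.** Also true. The trial enrols Wagner I–II or equivalent ulcers with adequate perfusion and no current infection, so real SAE risks may be lower than those assumed. The article also ascribes antimicrobial activity to the product, so an excess of infections is not a prediction. Power of 0.37 for 10% against 30% shows that even an all-cause count is weak at this size. That is a reason not to weaken it further.

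**The safety objective is to evaluate, not to compare.** The phrase about comparison with placebo belongs to the primary efficacy objective, so a formal safety comparison should not be read into the objective. The objective is still wider than the endpoint.

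**Conclusion.** The point holds as a mismatch between a stated endpoint and a stated objective. Under either reading, non-serious systemic AEs cannot enter the endpoint, and systemic SAEs enter only if judged related. Whether local wound events are filtered too is ambiguous.

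The consequence is dilution of any dose-versus-placebo difference in this one secondary endpoint, in proportion to the share of events judged related. It is not bias between arms and not loss of data. Its actual size cannot be derived from the document. The fall in power from 0.71 to 0.24 and 0.04 rests on assumed SAE risks of 10% and 40%, 30 patients per arm, attribution shares of a half and a quarter that are equal across arms, and events that are subject to the causality condition. The change is modest in scope but worth making, because it costs little.

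**What to change.** In Study endpoints, replace the adverse-event item with two counts by randomized arm, both regardless of causality: the number of patients with any treatment-emergent AE, and the number of patients with any SAE. Keep local AEs and SAEs judged related as sub-categories, and state whether the causality condition applies to local AEs.

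The cost is the endpoint wording and a few table rows. Table 3 already records adverse events from visit 2, the visit of the first application, so no new data, visits or patients are needed. If the analysis plan already tabulates all-cause AEs and SAEs by arm, only the wording changes.
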